### Sample Size and Variables

The total sample size will be 108 participants (27 in each of 4 groups).

The independent variables include Mulligan mobilization, Maitland mobilization, HVT, and MET. The dependent variables include pain (measured by the VAS), functional disability (measured by the MODI), and COG displacement (measured using a force plate; measurements will include sway velocity, lift-up index on the left and right, COG alignment, movement time, and impact index). Cointerventions include lumbar stabilization exercises and the application of hot moist packs.

### Procedure

Patients with low back pain presenting to Acharya Vinoba Bhave Rural Hospital, Sawangi (Meghe), Wardha, or the Musculoskeletal Outpatient Department, Ravi Nair Physiotherapy College, will be assessed for SIJ dysfunction, and their diagnosis will be confirmed through investigations and physical examination following approval from the institution’s ethics committee. Patients who meet all inclusion criteria and none of the exclusion criteria will be invited to participate in this study. In total, 108 participants will be enrolled after providing informed written consent. Demographic information will be gathered, and the baseline VAS score, MODI score, and COG displacement will be assessed for each participant. Then, participants will be randomized into 4 groups: group A (Mulligan mobilization), group B (Maitland mobilization), group C (HVT), and group D (MET). Each group will receive the assigned treatment 5 days per week for 3 weeks [6-8]. After 3 weeks of treatment, a postintervention evaluation will be conducted, and VAS scores, MODI scores, and COG displacement will be reassessed. These outcomes will also be reassessed two months after the intervention, at which point the data will be collected for analysis (see Textbox 1).

Textbox 1.Steps at each stage of the study.
**Prescreening**
Informed consent collectedPatients assessed by inclusion and exclusion criteria
**Baseline assessment (T0)**
Demographic information collectedPatients further assessed by inclusion and exclusion criteriaParticipants selected and randomized into 4 groupsPain assessed (visual analog scale [VAS])Disability assessed (Modified Oswestry Disability Index [MODI])Center-of-gravity (COG) displacement assessed (sway velocity, lift-up index, COG alignment, movement time, and impact index)Adverse events monitored for
**Intervention, 5 sessions per week for 3 weeks (T1)**
Intervention performed (moist heat treatment, manual therapy, lumbar stabilization exercises)Compliance check performed
**Postintervention assessment immediately after final intervention session (T2)**
Pain assessed (VAS)Disability assessed (MODI)Cog displacement assessed (sway velocity, lift-up index, COG alignment, movement time, and impact index)Adverse events monitored forCompliance check performed
**Follow-up, 2 months after final intervention session (T3)**
Pain assessed (VAS)Disability assessed (MODI)COG displacement assessed (sway velocity, lift-up index, COG alignment, movement time, and impact index)Adverse events monitored for

### Intervention

This study is designed to evaluate the therapeutic impact of different intervention protocols in patients with SIJ dysfunction. The study will include 4 intervention groups, each receiving conventional moist heat therapy, a manual therapy technique specific to each group, and lumbar stabilization exercises. Treatment sessions for all groups are designed to optimize outcomes and will occur 5 days per week for 3 weeks.

At the start of each session, participants in all groups will receive an identical moist heat treatment via commercial hot packs placed directly against the back for 10 minutes. Then, participants will receive the assigned manual therapy. Group A will receive Mulligan mobilization [9] to the sacral region, focusing on correcting SIJ alignment. Two distinct approaches will be used based on established protocols. These mobilizations will be delivered in 3 sets of 10 repetitions, with a 1-minute rest between sets. Group B will receive Maitland mobilization [8] in 3 sets of 30 seconds each. For the first 2 weeks, group B participants will receive grade 1 to grade 2 Maitland mobilization, and in the third week, grade 3 Maitland mobilization will be given. Group C will receive HVT [10,11], including anterior and posterior thrusts targeting the ilium, administered with the participant positioned supine or in a side-lying position. Specific maneuvers will also be used to correct up-slip and down-slip of the ilium using rapid, controlled thrusts applied by the clinician to restore joint alignment. Group D will receive MET [12,13] to correct anterior SIJ dysfunction, with the participant lying in a lateral position on the unaffected side with the affected leg flexed to the point of initial tension. A contraction intensity of 20% will be used.

After manual therapy, all groups will receive an identical structured lumbar stabilization exercise regimen [14]. This will comprise stretching exercises targeting muscles in the gluteal area, including the piriformis, gluteus medius, minimus, and maximus muscles, and SIJ self-mobilization techniques. Isometric hip muscle strengthening will be incorporated through exercises such as leg presses against a pillow and lateral leg pushes. Lumbar stabilization will be addressed via quadriceps and hamstring stretches, posterior pelvic tilts, standard back bridges with 1 and 2 legs elevated, and sit-ups. These exercises will be prescribed as 2 sets with a 1-minute rest interval between sets. These exercises will be performed 5 days per week in the clinic setting and twice daily at home.

Across all groups, interventions will be structured to ensure consistency of treatment delivery over the 3-week study period. Moist heat will be applied to facilitate tissue relaxation and enhance blood flow before manual therapy. Each manual therapy method has been selected for its documented efficacy in restoring SIJ mobility and alignment. The stabilization exercises will target muscular balance and postural control to improve functional outcomes, while the home exercise program will reinforce therapy gains outside clinical sessions.

### Criteria for Treatment Termination

Treatment will be terminated under specific circumstances for individual participants in each group. Treatment will be terminated for a participant (1) in group A if the participant is unable to actively participate or follow self-maintenance techniques, (2) in group B if symptoms are aggravated by passive movement, that is, if the participant experiences hyperreactivity to passive movement, (3) in group C if the participant experiences negative neurological change, feelings of fear, or excessive joint movement after HVT manipulation, or (4) in group D if the participant experiences muscle guarding or is unable to perform isometric contractions.

### Outcomes

The primary outcomes are changes in pain and disability. The subjective experience of pain will be measured using the VAS (*r*=0.94; *P*<.001) [15]. Participants will be shown the VAS, a 10-cm scale representing levels of pain, where 0 represents no pain and 10 represents unbearable pain, and asked to indicate their current level of pain. Functional disability will be measured using the MODI (*r*=0.87; *P*<.05) [16,17], a questionnaire that provides an assessment of the effect of low back pain on daily life. The score is calculated on a scale of 0% to 100% based on responses to the questionnaire.

The secondary outcome is change in COG displacement from the baseline, measured using a force plate. This will be measured at baseline, after 3 weeks of treatment, and at the 2-month follow-up using a force plate, which will be calibrated every 6 months by a biomedical technician. The force plate will be connected to a personal computer on which COG analysis software is installed. Participants will be asked to remove their footwear, stand on the force plate with their feet positioned on the designated markings, and distribute their weight equally between both feet. Participants will be asked to stand still for 30 seconds while the force plate measures sway velocity, lift-up index on the left and right, COG alignment, movement time, and impact index.

All outcomes will be assessed before the 3-week treatment begins, after three weeks of treatment, and at follow-up 2 months after treatment ends. The primary end points will be the change in all pain and disability from baseline to the 2-month follow-up, and the secondary end point will be the change in COG displacement from baseline to the 2-month follow-up. Changes in outcomes will be compared among the 4 groups after the 2-month follow-up.

### Data Analysis

Statistical analyses will be carried out using SPSS software (version 25.0; IBM Corp). To determine the significance of the differences between the 4 groups, we will first establish normality and then choose which test to use based on the distribution of the data. We will use mixed-design ANOVA if the data are normally distributed and the Friedman test if the data are not normally distributed. Statistical analysis will use a linear mixed-effects model for group-by-time interaction. Analyses will follow the intention-to-treat principle. Missing data will be handled by the missing-at-random assumption using maximum likelihood estimation. Planned pairwise comparisons will be adjusted for multiple testing using the Holm method. Repeated-measures ANOVA will be used to determine the significance of changes among the baseline, postintervention, and follow-up assessments. Frequency distribution and descriptive statistics will be used to analyze demographic information. For all statistical tests, *P*<.05 will be considered statistically significant, and 95% CIs will be reported.

Data collection and reporting will be performed under the guidance of the principal investigators, and documentation for the analysis will be reviewed for accuracy. An Excel spreadsheet containing the study data will be provided to a statistician who will be blinded to treatment allocation for statistical analysis after study completion. The trial data will be stored in a secure, locked location for later analysis by a biostatistician and the primary researcher (NC).

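### The Friedman test, named as the non-normal fallback for comparing the four arms, cannot compare independent arms, and the plan does not say that the mixed model decides

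*Protocol article*

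**What the plan says.** All of the analysis rules stand in one paragraph of the protocol article (Methods, Data Analysis).

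- **Purpose of the rule:** "To determine the significance of the differences between the 4 groups, we will first establish normality and then choose which test to use".
- **The rule:** "We will use mixed-design ANOVA if the data are normally distributed and the Friedman test if the data are not normally distributed".
- **A further model, with no normality condition:** "Statistical analysis will use a linear mixed-effects model for group-by-time interaction".
- **Population and missing data:** "Analyses will follow the intention-to-treat principle", and "Missing data will be handled by the missing-at-random assumption using maximum likelihood estimation".
- **Pairwise tests:** "Planned pairwise comparisons will be adjusted for multiple testing using the Holm method".
- **Change over time, as a separate question:** "Repeated-measures ANOVA will be used to determine the significance of changes among the baseline, postintervention, and follow-up assessments".

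Elsewhere, Study Design describes a four-arm parallel-group superiority trial. Sample Size and Variables gives 27 participants in each of 4 groups, 108 in all. Outcomes sets the primary end points as change in pain and disability from baseline (T0) to the 2-month follow-up (T3), compared among the four groups. The Discussion expects pain and disability to fall in every arm.

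**The concern.** The normality rule is tied explicitly to the between-arm question. It cannot be read as a fallback for change within arms, because change over time has its own test later in the paragraph. Friedman ranks related measurements within a block, so it is not a rank-based counterpart of a mixed-design ANOVA.

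If the data fail the normality check and the rule is followed, a p-value that reflects improvement common to all arms could be reported as a difference between techniques. The trial aims to rank the four techniques, and this test carries no information on that.

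The paragraph also leaves open how the gated rule relates to the mixed model. The analysis that decides the primary comparison could therefore be chosen after the data are seen.

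**Working it through.** **Inputs from the protocol article.** 4 × 27 = 108, which agrees with the stated total. Three assessments (T0; T2, after treatment; T3), significance level .05, improvement expected in every arm. **Assumed, because the article gives no such figures:** SD 1.5 VAS points, baseline mean 6, within-person correlation 0.5.

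**1. Friedman over the three visits, by hand.** With N = 108 participants, k = 3 visits and mean ranks r̄ⱼ,

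Q = [12N / (k(k+1))] Σ(r̄ⱼ − 2)² = (12 × 108 / 12) Σ(r̄ⱼ − 2)² = 108 Σ(r̄ⱼ − 2)².

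Arm does not appear in this formula, so relabelling the arms leaves Q unchanged.

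Now let every arm improve by 1 point at T2 and T3.
- SD of a between-visit difference: 1.5 × √(2 × (1 − 0.5)) = 1.5.
- Chance that a participant's T0 score exceeds a later one: Φ(1/1.5) = 0.7475.
- Expected mean rank at T0: 1 + 2 × 0.7475 = 2.495. At T2 and T3: (6 − 2.495)/2 = 1.7525 each.
- Q at these ranks: 108 × (0.495² + 2 × 0.2475²) = 108 × 0.3675 = 39.7, against a 5% critical value of 5.99 (2 degrees of freedom).

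The statistic is far beyond its critical value although the arms do not differ.

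**2. Simulation, 2,000 replicates per scenario, 27 per arm.** Percentage with p < .05:

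| Scenario | Friedman over visits | Kruskal-Wallis on T3−T0 | ANOVA on T3−T0 |
|---|---|---|---|
| All arms improve by 2, no arm difference | 100 | 4.9 | 5.3 |
| All arms improve by 1, no arm difference | 100 | 5.1 | 4.8 |
| No change, no arm difference | 5.0 | 4.6 | 5.1 |
| Two arms −1.5, two arms +1.5 | 1.5 | 100 | 100 |

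The first two rows match the protocol's expectation of improvement everywhere. The last row only illustrates the mechanism: its arm effects cancel and two arms worsen, so 1.5% is not a forecast for this trial.

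**3. Friedman with the four arms as columns.** Each row must then hold one participant from each arm, and the design provides no such pairing. For one simulated data set with Kruskal-Wallis p = 0.021, re-pairing the rows at random gave Friedman p-values whose central 95% ran from 0.003 to 0.24, with 57% below .05.

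**4. Reaching the Friedman branch.** If normality is tested at .05 in 12 arm-by-visit cells, truly normal data give at least one rejection with probability 1 − 0.95¹² = 46%. With 4 cells it is 1 − 0.95⁴ = 19%. Independence and the number of cells are assumed.

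**5. The ANOVA branch, only if run on complete cases.** Retained participants are 108 × (1 − d). At assumed loss d of 5, 10, 15 and 20% this is about 103, 97, 92 and 86. In a two-arm illustration with loss depending on the T2 score (14% and 22% lost, equal correlations of 0.6), the complete-case difference was 1.005 and the likelihood-based one 1.004, against 1.003 in the full data. So this step shows lost participants and a possible conflict with the stated policy; it does not show bias.

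**The case against.** The strongest reply is that a valid between-arm analysis is already named. The sentence after the rule gives a linear mixed-effects model without any normality condition, followed by intention to treat, maximum likelihood and Holm-adjusted pairwise tests. This stands. A reader might infer that non-normal data would leave the trial silent on which technique is better. That follows only if Friedman displaces the mixed model, which the article does not say.

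A reader might also infer that the ANOVA branch contradicts the intention-to-treat and maximum-likelihood policy. The article does not say that incomplete cases are dropped. Listwise deletion belongs to the classical repeated-measures procedure, and if the mixed-design ANOVA is fitted as the mixed model there is no contradiction. The retained counts also overstate the loss relative to that model, since a participant with baseline only adds almost nothing to the T0-to-T3 contrast.

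Nor do three analyses compete for one question. ANOVA and Friedman are alternative branches, and the repeated-measures ANOVA has its own purpose.

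Finally, how often normality would be rejected is unknown. VAS and MODI are bounded at 0, so skew after improvement is plausible, but the article gives no means or SDs.

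None of this repairs the rule itself. No passage makes Friedman a test of independent arms, and the generous reading of the ANOVA does not help it: Friedman also needs complete rows and uses no maximum likelihood.

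**Conclusion.** The rule is wrong as written. Friedman is assigned to the comparison of four independent arms and cannot make it. If it were used over visits and read as the plan labels it, equal improvement in all arms would be declared a group difference in about 100% of trials, against about 5% for a valid test on change. That size rests on the assumed SD, correlation and improvement of 1 or 2 points. The absence of an arm term rests on no assumption.

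The second defect is that the paragraph does not say whether the gated rule or the mixed model decides the between-arm question. A conflict between the ANOVA and the missing-data policy is conditional on a complete-case procedure and is not established by the text.

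Because the rule governs the primary comparison, it should be corrected before any analysis.

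**What to change.** 1. Delete the normality gate and the Friedman test as means of testing group differences, and with them the mixed-design ANOVA as a separate between-arm analysis.
2. State that the linear mixed-effects model already named is the sole primary between-arm analysis for VAS and MODI whatever the distribution. It should include all randomised participants with their available data, group-by-time terms, the baseline-to-2-month contrast and Holm-adjusted pairwise comparisons.
3. If a rank-based check is wanted, use one valid for independent arms, for example Kruskal-Wallis on the T0-to-T3 change. Call it a sensitivity analysis and label it as restricted to participants with T3 data, because it excludes anyone without that visit.
4. The repeated-measures ANOVA may keep its stated purpose of describing change over time, provided that it is not offered as evidence of a difference between arms.

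The cost is wording in the protocol or analysis plan. No new data, visits or participants are needed. The article expects follow-up to end in October 2026, so on that timetable the change can be made and dated before analysis.

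### The group-by-time interaction does not isolate the primary endpoint: the plan should name the arm contrast at 2 months as the primary test

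*Protocol article*

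**What the plan says.** The Outcomes section of the protocol article states the endpoint: "The primary end points will be the change in all pain and disability from baseline to the 2-month follow-up". It continues: "Changes in outcomes will be compared among the 4 groups after the 2-month follow-up". There are three measurement occasions: "All outcomes will be assessed before the 3-week treatment begins, after three weeks of treatment, and at follow-up 2 months after treatment ends". Textbox 1 labels them T0, T2 and T3, with T2 taken directly after the last treatment session.

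The Data Analysis section names several methods without ranking them:
- On the choice of test by distribution, it says: "We will use mixed-design ANOVA if the data are normally distributed and the Friedman test if the data are not normally distributed".
- On the model, without mention of a visit or contrast: "Statistical analysis will use a linear mixed-effects model for group-by-time interaction".
- On multiplicity, again with no visit given: "Planned pairwise comparisons will be adjusted for multiple testing using the Holm method".
- On change over time, with baseline as one of the levels: "Repeated-measures ANOVA will be used to determine the significance of changes among the baseline, postintervention, and follow-up assessments".

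None of these sentences names the baseline-to-2-month contrast as the primary test. None says at which visit the pairwise comparisons are made. The last one lists baseline as a level of time for the repeated-measures ANOVA; for the mixed model, the role of baseline is not stated.

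**The concern.** The endpoint concerns one visit, while the named test pools visits. An interaction over three visits asks whether the arms' profiles differ anywhere, not whether the arms differ at 2 months. Because T2 falls immediately after the final session, an early difference that fades before T3 is a realistic pattern. The Introduction says the trial will rank the four techniques. A significant interaction could then be read as support for a ranking although the arms do not differ on the declared primary endpoint. This is a mismatch between two things the article states, not a detail that it merely leaves to a fuller document.

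**Working it through.** **Inputs from the article.** Four arms, 27 per arm (108 = 4 × 27), three visits, significance level 0.05.

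**Assumed, because the article gives no values.** Within-person correlation rho = 0.3, 0.5 or 0.7, equal between all visits; SD of 1 at each visit; one arm differing from the other three; no missing data. The article gives no power or effect size, so there is no figure of its own to reproduce.

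**Reading 1: T0, T2 and T3 are all levels of time.**

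Degrees of freedom are (4 − 1) × (3 − 1) = 6. Three concern T3 − T0; the other three bring in T2.

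Let one arm differ by d2 at T2 and d3 at T3. The between-arm spread is 27 × (1 − 1/4) = 20.25 per squared unit of difference. The noncentrality parameters are:
- interaction, 6 df: 20.25 × (2/3)(d2² − d2·d3 + d3²) / (1 − rho)
- T3 − T0 change, 3 df: 20.25 × d3² / [2(1 − rho)]

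Effect at T2 only (d2 = 0.8, d3 = 0):
- interaction: 20.25 × (2/3) × 0.64 / (1 − rho) = 8.64 / (1 − rho), which is 12.34, 17.28 and 28.80
- T3 − T0 change: 0, so it rejects at its nominal level

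Rejection rates for a T2-only effect (10,000 simulated trials per scenario):

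| Test | rho 0.3 | rho 0.5 | rho 0.7 |
|---|---|---|---|
| Interaction, split-plot F, 0.8 SD | 74% | 89% | 99% |
| Interaction, multivariate (Wilks), 0.8 SD | 73% | 88% | 99% |
| Interaction, split-plot F, 0.5 SD | 32% | 44% | 68% |
| T3 test (change score or baseline-adjusted) | about 5% | about 5% | about 5% |

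The noncentral F calculation for 0.8 SD gives 74%, 89% and 99%, in agreement. With no effect anywhere, all tests reject in about 5%, so the interaction test itself is valid; it answers a broader question.

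**Reading 2: time covers T2 and T3, baseline is a covariate.**

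The interaction now tests whether arm differences change between T2 and T3. If one arm is better by the same amount at both visits, the T3 − T2 difference is 0.8 − 0.8 = 0 in expectation. The interaction then rejects at only 5%, however large the sustained benefit. This is not the endpoint either.

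**Does the 6-df test lose power for a real T3 effect?**

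Effect at T3 only (d2 = 0, d3 = 0.8):
- interaction: noncentrality 8.64 / (1 − rho) on 6 df; power 74%, 89%, 99% (multivariate version about 73%, 88%, 99%)
- 3-df change test: 20.25 × 0.64 / [2(1 − rho)] = 6.48 / (1 − rho); power 71%, 86%, 98%
- 3-df baseline-adjusted test: power 89%, 94%, 99%

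The interaction loses nothing to the change test in this pattern. The gap to the third line comes from baseline adjustment. An effect of 0.4 SD at T2 and 0.8 SD at T3 does show a loss: both noncentralities equal 6.48 / (1 − rho), and power is 59%, 76%, 95% for the 6-df test against 71%, 86%, 98% for the 3-df test. So the loss depends on the pattern.

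**Value of baseline adjustment, if the T3 contrast were an unadjusted change score.**

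Change-score variance is 2(1 − rho); baseline-adjusted variance is 1 − rho². The ratio adjusted/unadjusted is (1 + rho)/2 = 0.65, 0.75, 0.85.

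**The case against.** The strongest reply is that the contrast is already there. The group differences in T3 − T0 change can be obtained from the named mixed model, the Outcomes section says changes are compared among the arms after the 2-month visit, and Holm-adjusted pairwise comparisons with 95% CIs are planned. A reader might infer that the plan does not test its primary endpoint at all; the documents do not support that. What stands is that the Data Analysis section neither names this contrast as primary nor attaches the pairwise comparisons to it.

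A reader might also treat the interaction as the declared headline test. The article ranks none of its methods, so that hierarchy is not stated. But the absence of a ranking leaves the decisive test open, which is the point.

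A third inference would be that the plan ignores baseline. The article is silent on how the mixed model treats it: as a response level, a constrained level or a covariate. A condensed article may leave this to a fuller document, and a model with baseline as a response does not ignore it. Baseline adjustment therefore belongs in the recommendation and is not a charge of error.

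Finally, one might claim that power for a T3-only effect is lost by spreading over 6 df. The calculation shows otherwise for that pattern.

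**Conclusion.** The concern stands as a mismatch of specification. The stated endpoint is the change to 2 months; the named interaction does not isolate it on either reading of the time factor, and nothing ties the pairwise comparisons to that visit.

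The size is conditional. Given a T2-only advantage of 0.8 SD in one arm and no T3 difference, the three-level interaction is significant in about 73%, 88% and 99% of trials at rho 0.3, 0.5 and 0.7. These figures rest on assumed correlations, effect size and pattern, equal variances and complete data. They show what the test responds to and do not predict this trial. The coefficients of 0.94 and 0.87 in the Outcomes section are given as properties of the scales and cannot stand in for baseline-to-2-month correlations.

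The possible gain from baseline adjustment (variance 0.65, 0.75 or 0.85 of the unadjusted change score) applies only if the contrast would otherwise be unadjusted.

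**What to change.** For each primary outcome (VAS and MODI), state in the Data Analysis section:

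- **Primary test:** the 3-df comparison of the four arms at 2 months, taken from the linear mixed-effects model.
- **Baseline:** adjust for the baseline score already collected (with a baseline-by-visit term), or keep baseline as a response with its mean constrained equal across arms. Say which.
- **Pairwise comparisons:** the six arm contrasts at 2 months, Holm-adjusted, with 95% CIs.
- **Secondary:** contrasts at T2 and the overall group-by-time interaction.

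The cost is a few sentences and no new data. The Results section expects follow-up to end in October 2026, so the wording can be fixed before the final data are analysed.

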Although each technique is well established individually, no comparative study has been conducted to evaluate the relative efficacy of these manual therapy approaches. A comparative analysis of these techniques could provide valuable evidence to guide clinical decision-making and optimize treatment outcomes for individuals with SIJ dysfunction.

This study aims to compare the efficacy of Mulligan mobilization, Maitland mobilization, HVT, and muscle energy technique (MET) in improving pain, functional disability, and COG displacement in patients with SIJ dysfunction and to rank these approaches according to their efficacy.

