### Participant Recruitment

Participants who meet the inclusion criteria will be enrolled in this study. A computer-generated randomization sequence will be used to randomly allocate participants to 4 groups in a 1:1:1:1 ratio. The sequence will be generated by a supervisor (LL) who will not be involved in recruitment or treatment. The allocation sequence will be placed in sequentially numbered, opaque, sealed envelopes by the supervisor. The envelopes will be stored in a locked cabinet until they are opened by the treating therapist immediately prior to treatment. Participants will be blinded to group allocation and the specific manual therapy technique received. All interventions will be delivered in the same clinical setting with standardized session duration. Outcomes will be assessed by an independent assessor who will be blinded to treatment allocation. The treating therapist will not be involved in outcome assessment. Unblinding will not be permitted for the participants or assessor.

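### Plain Holm is valid for the pairwise comparisons, but if the family is all six pairs of the four arms, Shaffer's step-down gives slightly more power under the same 5% familywise bound

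*Protocol article*

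**What the plan says.** The protocol article fixes the multiplicity method in Data Analysis: "Planned pairwise comparisons will be adjusted for multiple testing using the Holm method". The significance level is given in the same section: P "<.05 will be considered statistically significant, and 95% CIs will be reported". It does not say how many pairs are planned, or whether the family is formed for each outcome or pooled.

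Three other places bear on which pairs are meant:
- The Introduction gives the aim of comparing the four techniques and "to rank these approaches according to their efficacy".
- Participant Recruitment will "randomly allocate participants to 4 groups in a 1:1:1:1 ratio". Sample Size and Variables gives 27 per group, 108 in all. No arm is called the reference.
- Outcomes says: "Changes in outcomes will be compared among the 4 groups after the 2-month follow-up". It names two primary outcomes: "The primary outcomes are changes in pain and disability".

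**The concern.** Holm's method treats the hypotheses as if any number of them could be true together. Pairwise equalities of four means are linked: if A equals B and B equals C, then A equals C. Some counts of true equalities are therefore impossible, and a procedure that protects against them spends alpha for nothing.

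The loss falls where this trial's aim is most demanding. Showing that one technique is better than each of the other three takes three rejections, and a fuller ranking takes more. The affected steps are the second and third. With 27 per arm, power that costs nothing is worth taking.

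**Working it through.** **Inputs.** From the article: 4 arms, 27 per arm, alpha 0.05, Holm. Assumed: two-sided tests (sidedness is not stated); a family of all 4 × 3 / 2 = 6 pairs for one outcome; normal data with common SD, no missing values, pooled-variance t tests with 108 − 4 = 104 df. The article gives no effect size, SD or power, so effects are assumed in SD units and shown as a range. The only design figure that can be reproduced is 4 × 27 = 108, which is consistent.

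**Step 1: how many of the six equalities can be true together.** Group the four means by equality and count the equal pairs.

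| Grouping | True equalities |
|---|---|
| all four equal | 6 |
| three equal, one apart | 3 |
| two and two | 2 |
| one equal pair, two apart | 1 |
| all different | 0 |

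The attainable counts are 0, 1, 2, 3 and 6. Four or five cannot occur.

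**Step 2: divisors.** At step j, with 7 − j hypotheses left, Holm divides alpha by 7 − j. Shaffer divides by the largest attainable count not exceeding 7 − j.

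| Step | Left | Holm threshold | Shaffer threshold |
|---|---|---|---|
| 1 | 6 | 0.05/6 = 0.0083 | 0.05/6 = 0.0083 |
| 2 | 5 | 0.05/5 = 0.0100 | 0.05/3 = 0.0167 |
| 3 | 4 | 0.05/4 = 0.0125 | 0.05/3 = 0.0167 |
| 4 | 3 | 0.05/3 = 0.0167 | 0.05/3 = 0.0167 |
| 5 | 2 | 0.05/2 = 0.0250 | 0.05/2 = 0.0250 |
| 6 | 1 | 0.0500 | 0.0500 |

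Only steps 2 and 3 change, and no Shaffer divisor exceeds Holm's. Every Holm rejection is therefore also a Shaffer rejection.

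**Step 3: error control.** Let m0 equalities be true, and let the first false rejection come at step j. The j − 1 earlier rejections were all of false hypotheses, so m0 is at most 7 − j. Because m0 is an attainable count, the Shaffer divisor at step j is at least m0. A false rejection thus requires some true hypothesis to have P ≤ 0.05/m0, and by Bonferroni that has probability at most 0.05. The argument needs only valid P values.

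**Step 4: size of the gain.** Both methods were applied to the same simulated trials, with one arm better than three equal arms.

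| Advantage | Better than all three: Holm | Better than all three: Shaffer | Trials with at least one extra rejection |
|---|---|---|---|
| 0.3 SD | 1.1% | 1.5% | under 3% |
| 0.5 SD | 7.1% | 8.9% | about 7% |
| 0.8 SD | 41.6% | 46.3% | about 11% |
| 1.0 SD | 72.7% | 76.4% | about 7% |

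Repeat runs moved the power figures by up to 0.4 of a percentage point. Shaffer never rejected fewer hypotheses in any simulated trial. Familywise error with all arms equal was 4.1% for both. At 0.8 SD it rose from about 3.3% to 4.2%. The largest value in any configuration examined was 4.98%, and there the two methods gave the same figure. The chance of at least one true rejection hardly moved: 39.1% v 39.2% at 0.5 SD and 82.8% for both at 0.8 SD.

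**Step 5: the same gain as a detectable difference.** At a threshold of 0.05/d, the difference detectable with 80% power is (z for two-sided 0.05/d + 0.842) × √(2/27).
- Holm, step 2 (d = 5): (2.576 + 0.842) × 0.272 = 0.930 SD.
- Shaffer, step 2 (d = 3): (2.394 + 0.842) × 0.272 = 0.881 SD.

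The ratio squared is (0.930/0.881)² = 1.11. Matching Shaffer at that step under Holm would take about 11% more participants, roughly 3 per arm.

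**The case against.** The strongest reply is that nothing here is wrong. Holm controls familywise error under any dependence, and the choice between two valid methods could be called preference. That Holm is valid stands in full. A reader might infer that the planned adjustment is faulty or anti-conservative, and the document does not support that. What takes the point beyond preference is that, for the six-pair family, one method dominates the other at no cost in data or sample size.

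Second, the number six is inferred. Data Analysis speaks only of planned pairwise comparisons. The family might be a subset, be pooled over pain and disability, or include more than one time point. This also stands. Holm is safe for any family, while the sequence 6, 3, 3, 3, 2, 1 is valid only for one complete set of six pairs and would not control the error rate in a larger or mixed family. The recommendation therefore depends on declaring the family first.

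Third, the gain looks best at large effects. All four arms are active, share the same heat and exercise treatment, and are all expected to improve, so differences between them may be modest. At 0.3 to 0.5 SD the gain in the chance of beating all three others is under 2 percentage points. A reader might take the change as a remedy for low power; it is not, because the first step is the same under both methods.

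Fourth, a reader might say that the error rate stays the same. Only the 5% bound does; the realised rate moves closer to it.

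Finally, the simulation uses complete normal data, whereas the article says: "Statistical analysis will use a linear mixed-effects model for group-by-time interaction", with missing data expected. That would change the percentages. It would not change the ordering of the two methods, which rests on steps 2 and 3 of the working.

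**Conclusion.** The point holds as a minor improvement that costs nothing, not as a correction. For a family of all six pairs, which is the natural reading of the ranking aim but is not stated, Holm's divisors of 5 and 4 are stricter than needed, and Shaffer's procedure is uniformly at least as powerful under the same 5% bound. The dominance and the bound are exact. The size of the gain is conditional on 27 per arm, two-sided tests, complete normal data and assumed effects: about 4 to 5 percentage points in the chance of separating one arm from the other three at 0.8 to 1.0 SD, and less than 2 points at 0.5 SD or below.

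**What to change.** In Data Analysis, replace the sentence on Holm with wording such as: for each primary outcome, the family is the six pairwise contrasts between arms in change from baseline to the 2-month follow-up, adjusted by Shaffer's step-down procedure at two-sided familywise 5%, with ordered P values compared with alpha/6, alpha/3, alpha/3, alpha/3, alpha/2 and alpha, stopping at the first non-rejection.

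If one family is to cover both primary outcomes, the attainable counts are sums of two values from 0, 1, 2, 3 and 6, that is 0 to 9 and 12. The divisors then begin 12, 9, 9, 9, 8, 7. For any other family (a subset of pairs, or added time points) they must be re-derived. If the family is to stay open, keep Holm.

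The cost is a sentence or two and different divisors on the same ordered P values. Data collection, model, visits and sample size are untouched. The change should be written down before any outcome data are seen by group. The article leaves room for that: 63 of 108 participants had been recruited by November 2025, follow-up is expected to end by October 2026, and the blinded statistician receives the data after completion.
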